### Interventions

The entire treatment involves 20 consecutive sessions of home-based self-administered tDCS, one session per day. Initially, the participants will receive orientation about how to use the remote tDCS device. One physical therapist will instruct the participants about the tDCS protocol, download the application and demonstrate how to handle the device, including the position on the head, and operate it using the smartphone application. The Samphire App for IOS will be used. The training will also include the best practices for device preservation and conservation, such as leaving the tDCS in a safe place, and not over-exposing it to the sun or a heat source. Moreover, the researcher will inform the risks and guidelines related to potential expected adverse effects of use, which include redness at the site, itching where the electrodes are in contact with the skin, headaches after use, dizziness or nausea. The researcher will configure the smartphone application to be accessible in the participants’ native language (Brazilian Portuguese), with an option to switch to English. After training, participants will receive the device to use alone, according to instructions.

### tDCS

The Samphire Neuroscience tDCS will be used. The device has four rectangular sponges (5.0 cm × 2.0 cm and 2.5 mm thickness) that must be impregnated by the user with a saline (0.9% NaCl) solution before placing the tDCS on the head. The two anode electrodes will be placed in the region of the M1 and the DLPFC of the left cerebral hemisphere, at points C3 and FC5, respectively. The two cathode electrodes will be placed under the same regions of the right hemisphere, C4 and FC6, according to the international electroencephalography (EEG) 10/20 system. Each participant will self-administer it during 20 sessions for 20 minutes per session. In the active tDCS group, the current will ramp up from 0 to 2.0 mA over 30 s, and ramp down over 30 s, for a 20 min total session time. In the sham tDCS group, to ensure blindness, the current will ramp up to 2.0 mA over 30 s, then ramp down to 0.01 mA, over 30 s. This method produces the same mimic sensations, such as itching and tingling observed during active tDCS, enabling blindness.^21^ Both active and sham tDCS groups will use identical tDCS devices and use the same App. The session type will be determined by a previous randomised code input into the Samphire App. During tDCS use, participants will receive instruction to feel free and continue with their habitual routine.

### Outcomes

The study will conduct evaluations at five time points, all scheduled to coincide with the onset of the first day of the menstrual cycle. The initial evaluation (baseline) will be conducted before any interventions occur, specifically on the first day of the participant’s first menstrual cycle. The second evaluation will occur after the completion of all 20 intervention sessions, specifically scheduled for the first day of the participant’s third menstrual cycle. Follow-up assessments will be conducted monthly, specifically on the first day of the participant’s third through fifth menstrual cycles. Figure 1 illustrates the evaluation process. The initial evaluation will include anamnesis, physical examination, pain assessment, and questionnaires.

**Figure 1 F1:**
[figure not shown]
Schedule of enrolment, interventions and assessments. 6MWT, six-minute walk test; BDI, Beck Depression Inventory; HAS, Hamilton Anxiety Scale; PANAS, Positive and Negative Affect Schedule; PGI, Patient Global Intervention; PSST, Premenstrual Symptoms Screening Tool; STT, TUG, Timed Up and Go; VAS, visual analogue scale; WHOQOL, WHO Quality of Life.

The primary outcome is pain and will be assessed through the Visual Analogue Scale (VAS). The VAS is a unidimensional measure of pain intensity, consisting of a continuous scale composed of a horizontal line, 10 centimeters (100 mm) in length, anchored by two verbal descriptors, one for each extreme symptom.^22^ The scale is anchored by ‘no pain’ (score of 0) and ‘worst imaginable pain’ (score of 100 (100 mm scale)). Participants will self-complete the VAS, instructed to mark a line at the point representing the intensity of their pain during the day. The VAS serves as a direct pain index commonly used in clinical investigations of acute and chronic pain in patients, owing to its convenience and reliability.^22^

The secondary outcomes will include algometry, quality of life (WHO Quality of Life Questionnaire (WHOQOL-Bref)), premenstrual symptoms (Premenstrual Symptoms Screening Tool (PSST)), depression (Beck Depression Inventory (BDI)), anxiety (Hamilton Anxiety Scale (HAS)), affectivity (Positive and Negative Affect Scale (PANAS)), physical performance (6 min walk test, 30 s sit-to-stand test, Timed ‘Up and Go’ and dorsal dynamometry) and level of satisfaction with the intervention (Patient Global Intervention (PGI)).

A digital pressure algometer (MedDor, Brazil) will evaluate the pain sensitivity, observing the threshold and tolerance to pressure pain and the perception of pain intensity. The same trained examiner will position the pressure algometer perpendicular to the skin three centimetres below the umbilicus.^23^ Then, the examiner will place the 1 centimetre-diameter rubber tip over the examination area and gradually increase the pressure by approximately 1 kg/cm^2^/s to measure the pressure pain threshold and pressure pain tolerance.^23^ The examiner will describe the pain threshold when the patient first reports the beginning of pain perception through the phrase ‘start’. Additionally, for pain tolerance, the participant will be instructed to endure the maximum pressure applied by the algometer until reporting total inability to withstand such pressure, signalling with the phrase ‘stop’.^23^ Participants must repeat exactly these two sentences for complete standardisation of the exam. To measure the perception of pain intensity, the examiner will apply a painful mechanical stimulus for 5 s, considering the mid-point between the pressure pain tolerance and pressure pain threshold data, previously obtained from each participant.

The WHOQOL-brief will assess quality of life.^24^ This questionnaire presents 26 questions, with the initial two questions focusing on general quality of life. The remaining questions are divided into four domains: (1) physical domain includes facets, such as pain and discomfort, energy and fatigue, sleep and rest, mobility, activities of daily living, dependence on medication or treatments and ability to work; (2) psychological domain covers facets, such as positive feelings, thinking, learning, memory and concentration, self-esteem, body image and appearance, negative feelings, spirituality, personal beliefs and religion; (3) social relationships address facets, such as personal relationships, social support and sexual activity; and (4) environmental domain encompasses facets, such as physical safety and protection, home environment, financial resources, health and social care (availability and quality), opportunities to acquire new information and skills, participation and opportunity for recreation and leisure, physical environment and transportation. A higher score indicates a better quality of life.^24^ This questionnaire is a helpful tool to assess the impact of primary dysmenorrhoea on participants’ quality of life, social and personal functioning, known to affect overall well-being.^25^

PSS is a tool developed by Steiner *et al*,^26^ translated and validated to Portuguese by Câmara *et al.*^27^ This tool has 14 questions related to the presence and intensity of symptoms related to premenstrual syndrome. Also, the questionnaire presents five questions that investigate the interference of premenstrual syndrome in daily activities and individual relationships. All items include a Likert-type scale, ranging from 0 to 4, with 0 representing absence, 1 indicating mild, 2 denoting moderate and 4 indicating severe.^27^ A positive result for premenstrual syndrome requires the following options: the presence of at least five items from the first domain, classified from moderate to severe; at least one of the four main symptoms (anger/irritation, anxiety/tension, desire to cry/increased sensitivity to rejection, depressed mood/hopelessness) classified as moderate or severe; and at least one item from the second domain classified as moderate or severe. Participants who do not meet the above requirements are, according to the PSS tool, classified as having no premenstrual symptoms or having mild symptoms.^27^ This tool is important due to the high comorbidity of premenstrual symptoms in women affected by primary dysmenorrhoea.

BDI will assess depression levels. We will use a self-administered Portuguese-language questionnaire consisting of 21 items assessing symptoms and cognitive attitudes. For each item, the patient must choose one or more statements that best describe how they felt in the last week. The maximum score is 63 points, and higher scores indicate severe levels of depression. A score less than 10 points indicates no or minimal depression; from 10 to 18 mild to moderate depression; from 19 to 29 moderate to severe depression; and from 30 to 63 severe depression.^28^

HAS will evaluate anxiety. This was one of the first rating scales developed to measure the severity of anxiety symptoms and is still widely used today in clinical and research settings. The scale has 14 items, ranging from 0 to 4, with a total score of 56. The higher the score, the greater the degree of anxiety.^29^

The PNAS will assess affectivity. This questionnaire consists of a set of 20 words that describe different feelings and emotions felt by the patient during the last 60 weeks. This questionnaire has two dimensions, using 10 words to calculate positive affectivity and 10 for negative affectivity. Each word is scored from 1 (not at all) to 5 (extremely), and the total scores can vary from 10 to 50 for each dimension.^30^

The questionnaires WHOQOL-Bref, PSST, BDI, HAS, PANAS and PGI will be administered using versions that have been translated, culturally adapted and validated for use in Brazilian Portuguese.

Four tests will assess physical performance: the 6MWT, the 30 s sit-to-stand test, the TUG and dorsal dynamometry. The 6MWT is an evaluation of the maximum distance covered by the patient during 6 min. The 6MWT is widely used to assess submaximal functional capacity.^31^ During the test, there will be two standardised phrases to encourage the patient, in the third and fifth minutes, aiming at increasing their physical performance. The parameters measured before and after the test will be the respiratory rate, heart rate, haemoglobin oxygen saturation, Borg scale, presence of pain, and total distance covered.

The 30 s sit-to-stand test aims to measure the lower limbs’ strength. There will be a stopwatch and a chair with a height of 43 cm with a backrest. The patient will sit in the middle of the chair with feet flat on the floor and arms crossed over the chest. The score will correspond to the number of times the person performs the complete movement in 30 s.^32^

The TU test measures the lower limbs’ muscular strength and includes power, speed, agility and dynamic balance. It provides a comprehensive assessment of general muscle strength and physical function. We will instruct the subjects to stand up from the sitting position at the examiner’s signal, walk a distance of 3 m in a comfortable place, turn around, walk back to the chair and sit down again.^33^

Dynamometry will assess the isometric strength of the trunk extensor muscles. To perform the test, the participant will stand on the dynamometer platform with their knees fully extended but not hyperextended. Then, the trunk will flex forward, forming an angle of approximately 120° between the trunk and lower limb. The participants will position their heads in the midline with their gaze fixed straight ahead and their elbows extended.^34^ The dynamometer handle will be adjusted according to the size of the participant so that he/she can hold the support bar to maintain the position described above. The grab bar must be close to knee height. After that, participants will use their spine extensors to pull the handle towards their trunk as strongly as possible. The Crown 200 kg dynamometer will record the resultant force. There will be three attempts to generate the data. The highest value will be retained for analysis.^34^ At the end of the procedure, the pain perception of participants will be evaluated using the numeric rating scale, ranging from 0 to 10.

An EEG will assess cerebral effects and modification of electrical patterns. Brain electrical activity will be recorded using OpenViBE Acquisition Server (v3.2.0 - 64bit) and OpenViBE Design (v3.2.0 - 64bit) software, employing a 32-channel EEG system (engineering model actiCHamp, Brain vision), with a sampling rate of 10 kHz. Electrodes will be placed according to the international 10–20 system on an elastic cap (actiCAP DE-82211 model, EASYCAP GmbH), which will be comfortably adjusted on the participants’ heads. Each of the 32 electrodes will be positioned at specific locations corresponding to the following brain areas: FP1, FP2, AFp1, AFp2, AFZ, AF3, AF4, AF8, AF7 (GND), AFF1h, AFF2h, Fz, F1, F2, F3, F4, F5, F6, F7, F8, FC1, FC2, FC5, FC6, CZ, C3, C4, P3, P4, P7, P8, O1 and O2. To minimise impedance, a conductive paste (SuperVisc gel - 1000 g, EASYCAP GmbH) will hold the electrodes. Additionally, there will be a reference electrode at Fz. During recording, participants will remain seated and will be instructed to avoid any unnecessary movements. Recording will take place in a quiet, dimly lit room to minimise recording artefacts. A computer will save the data for offline analysis. To ensure data quality, the following measures will be adopted: (1) impedance will be monitored during electrode placement to ensure it remains below 5 kOhm; (2) before recording commences, the researcher will check electrical noises; and (3) during recording, the responsible researcher will continuously monitor signal quality and check for movement artefacts, eye blinking or muscle activity. EEG will be conducted at baseline (T0), after the first tDCS session (T1) and after 20 tDCS sessions.

The patient’s global impression will measure the participants’ satisfaction. It is a simple evaluation method composed of a seven-item scale, ranging from one (no changes) to 7 (much better). Improvement throughout the treatment involves the personal and psychometric aspects inherent to the pain treatment process. This scale identifies minor clinically important changes, which are sometimes not noticed in pain questionnaires or physical examinations.^35^

### Participant timeline

Figure 1 shows a general schedule, including enrolment, intervention and follow-ups. In the first month, the research proposal and randomisation will be explained, and the menstrual cycle will be monitored to identify the first day of the next menstrual cycle. In the second month, on the first day of the menstrual cycle, the participants will be assessed as baseline (**T0**) and will receive instructions and training about the use of home-based self-administered tDCS. In the third month, participants will start the tDCS sessions 20 days before the estimated date of the first day of the menstrual cycle. The assessment (**T1**) of all variables will be performed on the first day of the menstrual cycle. For three consecutive cycles after tDCS intervention, participants will be assessed as follow-up always on the first day of each menstrual cycle (**T2, T3 and T4**). A total of five assessments will be performed. It is important to note that there will be five evaluation time points, always on the first day of the menstrual cycle.

Before starting the trial, all researchers involved will be trained for evaluations and tDCS procedures. Five researchers will be involved in this clinical trial: one researcher for the evaluation procedures, two for the home-based self-administered tDCS instruction and training (instructor), one for the randomisation of participants and one for statistical analysis.

### Sample size

The sample size will follow previous research conducted by our group. The numerical rating scale for pain is the primary outcome of assessing women affected by chronic pelvic pain. The participants also attended five sessions of tDCS using a C3/Fp2 assembly.^19^ G*Power (V. 3.1.9.4, Düsseldorf, Germany) estimated the power and sample size requirements through the use of the F-test from a repeated measures analysis of variance, including the main effects of group and time and the two-way interaction between group and time. Based on an alpha of 0.05 and power of 0.80, two groups (active group and sham group), sphericity of 1 and effect size of 0.25, a total of 34 participants will be required, with 17 participants randomised to each group. With anticipated attrition, we will add six more participants, totalling 40 participants (active group, n=20; sham group, n=20).

### Randomisation, allocation concealment and blinding

A numerical sequence generated by appropriate software will assign each participant to the active tDCS group or the sham tDCS group, using a 1:1 allocation ratio. Each participant will be equally likely to belong to any group. An independent researcher not involved in the assessment or intervention will conduct all processes. Allocation concealment will be performed using opaque envelopes. Volunteers and researchers involved in assessments and interventions will maintain blinding to the participants’ allocation throughout the study.

Additionally, all procedures regarding the use of home-based self-administered tDCS will be performed for the sham group. First, the participants will position the device and turn it on. Then, they must follow the instructions and use the smartphone application. However, the tDCS will administer 2 mA of current with a ramp-up and ramp-down period of 30 s. Sham tDCS will involve administering active stimulation for a brief duration to replicate sensations (itching and tingling) observed during active tDCS.^21^

To initiate the tDCS protocol, participants will receive a code via email to access the smartphone application, allowing them to unlock 20 sessions of tDCS (one per day). The allocation of active or sham stimulation will be known only to a single researcher not involved in assessments or intervention.

### Statistical analysis

SPSS software version 21.0 (IBM Corp., Armonk, NY, USA) will analyse the data. We will describe the clinical sociodemographic characteristics using mean and SD for continuous variables and frequency and percentage for dichotomous variables. Independent t-test and X^2^ will analyse continuous and categoric sociodemographic data, respectively. Intention-to-treat analysis will include the data from participants who do not complete the entire treatment protocol. We will define the significance level in all statistical testing as a p value less than 0.05. After data collection, we will identify the best distribution to represent the data according to the residuals Q–Q plot and histogram. The generalised estimated equations or mixed model will analyse the data (primary and secondary outcomes at baseline, after the fifth session, after the last session and follow-ups). We will also evaluate if it is necessary to insert fixed or random factors into the constant based on A/C, B/C and Q/C indices, X^2^/DF and the intraclass correlation coefficient. The link function will estimate the results according to the distribution of the dependent variable. Time, group (active and sham groups) and the interaction between them will represent the independent factors. The mean, mean difference, SD, 95% CI and p value for baseline, after the last session and follow-ups will illustrate the results. Cohen’ d will represent the effect size.

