**Methods and analysis:**

This is a single-centre, parallel, randomised, double-blinded clinical trial protocol. 40 women affected by primary dysmenorrhoea will be randomised into two groups (active-tDCS or sham-tDCS). Then, 20 consecutive sessions of home-based self-administered tDCS will be performed. The assessments will occur at five time points: baseline, after the 20th sessions, at the first, second and third cycles after tDCS interventions (follow-ups). Primary outcome will be pain according to visual analogue scale. Quality of life, premenstrual symptoms screening, depression, anxiety, physical performance, electroencephalography and participants’ satisfaction will be the secondary outcomes. A mixed analysis of variance will calculate the effect of stimulation.

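### No visit or model term is named as deciding for VAS pain, while 0.05 applies to every test; if any one of four visits could be claimed, the type I error would be about 15% (range about 9% to 19%)

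*Protocol article*

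**What the plan says.** The primary outcome is given as an instrument. The Abstract has "Primary outcome will be pain according to visual analogue scale", and the Outcomes section has "The primary outcome is pain and will be assessed through the Visual Analogue Scale (VAS". Neither adds a visit, a contrast or a summary over visits.

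The visits are set out in the Abstract: "The assessments will occur at five time points: baseline, after the 20th sessions, at the first, second and third cycles after tDCS interventions (follow-ups". Participant timeline labels them T0 (baseline), T1 (first assessment after the 20 sessions) and T2 to T4, which makes four assessments after baseline.

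Three sentences in Statistical analysis govern the testing:
- the model: "Time, group (active and sham groups) and the interaction between them will represent the independent factors";
- the reporting: "The mean, mean difference, SD, 95% CI and p value for baseline, after the last session and follow-ups will illustrate the results";
- the threshold: "We will define the significance level in all statistical testing as a p value less than 0.05".

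The Abstract says that a mixed analysis of variance will give the effect of stimulation. Statistical analysis says generalised estimating equations or a mixed model. Sample size uses a repeated-measures F-test and names both main effects and the interaction. None of the three picks out one term as the test of efficacy.

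**The concern.** A primary outcome measured at four visits becomes a single hypothesis only once the plan says which visit, which summary over visits or which model term carries the conclusion. Here the plan gives several p values for pain, all judged at 0.05, and no rule for combining them. A difference at T1 only, a difference at T3 only, a significant group effect or a significant interaction could each be presented as the primary result.

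This is more than a detail left to a later document. The article itself sets 0.05 for all testing and p values at several visits. A later rule that split alpha or named one contrast would alter that published rule. In a trial of 40 women, whether a positive claim can be believed depends on this choice having been made before the data are seen.

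**Working it through.** **Inputs from the article.** Alpha 0.05 for every test; four post-baseline visits; 20 per arm planned (17 per arm required); model terms group, time and interaction. For sample size: effect size f = 0.25, power 0.80, two groups, sphericity 1.

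**Input not given.** The correlation ρ between visits. It is treated as an assumption and varied from 0 to 0.9.

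**Step 1. The plan's own figure, N = 34.** For the group-by-time interaction with m measurements, the noncentrality is λ = f²·N·m/(1−ρ), with (m−1) and (N−2)(m−1) degrees of freedom. The article gives neither m nor ρ.
- m = 2, ρ = 0.50: λ = 0.0625 × 34 × 2/0.50 = 8.5; power 0.807; smallest even N = 34.
- m = 3, ρ = 0.40: λ = 0.0625 × 34 × 3/0.60 = 10.6; power 0.821; smallest even N = 34.
- m = 5, ρ = 0.15: λ = 0.0625 × 34 × 5/0.85 = 12.5; power 0.804; smallest even N = 34.

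The figure reproduces, but under several settings, so it does not reveal which contrast was meant to decide.

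**Step 2. Reference value for four visits.** With independent tests, P(at least one p < 0.05) = 1 − 0.95⁴ = 18.5%.

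**Step 3. Allowing for correlation.** The trial was simulated with no treatment effect: 20 per arm, five visits, two-sided t-tests at 0.05 at each post-baseline visit, 60,000 runs per setting.

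| Between-visit correlation (exchangeable) | Any of T1 to T4, raw scores | Any of T1 to T4, change from baseline |
|---|---|---|
| 0 | 18.6% | 15.5% |
| 0.3 | 17.5% | 15.5% |
| 0.5 | 15.7% | 15.6% |
| 0.7 | 13.1% | 15.5% |
| 0.8 | 11.7% | 15.7% |
| 0.9 | 9.2% | 15.8% |

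Under first-order autoregressive correlation of 0.5, 0.7 and 0.9, raw scores give 16.6%, 14.7% and 10.4%. Change scores give 14.3%, 14.1% and 13.1%. A numerical check with four equicorrelated normal tests gives 17.4%, 15.6%, 13.0% and 9.4% at ρ = 0.3, 0.5, 0.7 and 0.9, in agreement with the raw-score column.

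**Step 4. Model terms.** If either the group or the interaction term may be claimed, the error is about 9.7% (exchangeable). If any visit or either term may be claimed, it is 18.8% at ρ = 0.5, and 13% to 22% over the range.

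**Step 5. With a rule in place.** One pre-named test whose assumptions are met has 5% error. If visit tests count only after a significant interaction, the error when there is no effect at any visit is 0.8% to 4.0%. The uncorrected interaction F-test used alone gave 5.9% to 7.9% under the autoregressive patterns, because sphericity then fails.

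**The case against.** **The any-visit rule is not written anywhere.** This is correct. The plan describes a joint model, and the per-visit results are introduced as illustrating it. The list even includes baseline, where no efficacy claim is possible, and the text does not say whether the mean difference is between groups or over time. If the interaction were meant as a gate, the error would be at most about 4% when there is no effect. What stands is that the inflated figure is conditional. What does not follow is that 5% is protected, because no sentence makes the interaction decisive or a gate.

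**A condensed article may leave this to an analysis plan.** That would excuse silence. Here the article states a threshold for all testing together with p values at several visits, and it defines the primary outcome without a time point. The finding rests on that stated rule.

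**The number is not in the documents.** This is also correct: no between-visit correlation is given, and separate t-tests stand in for the planned model. The visit count is blurred too. Outcomes places both the second evaluation and the first follow-up in the third cycle, and Statistical analysis lists "primary and secondary outcomes at baseline, after the fifth session, after the last session and follow-ups", although no fifth-session visit is in the schedule. With three post-baseline tests the figure would be 14.3% if independent and about 12.6% at ρ = 0.5. The error stays well above 5% in every case.

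**Stronger readings that the article does not support.** A reader might infer that the trial was powered for a single pre-post contrast, so that the powered test is not the one the conclusion needs. Step 1 rules that inference out, since a three-visit or five-visit interaction also yields 34. A reader might also multiply the secondary measures by four visits and count expected false positives. That assumes every measure is tested at every follow-up. Participant timeline says all variables are assessed only for T1, and the schedule figure is not shown. These outcomes are labelled secondary, with no confirmatory claim attached.

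**Conclusion.** The point holds. Statistical analysis sets 0.05 for every test and gives p values for VAS pain at several visits plus model terms, without saying which result decides. As written, the plan does not hold the type I error on the primary outcome at 5%.

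The size is conditional on a significant difference at any one of T1 to T4 being claimed as success, which the text allows but does not announce. On that condition the error is about 15%, with a range of about 9% to 19%. The value depends on the between-visit correlation and on whether raw or change scores are compared. No setting tried brought it down to 5%. It would be 5% or less if one deciding test with its assumptions met, or a gate, had been named. The point does not depend on how N = 34 was obtained or on the number of secondary outcomes.

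**What to change.** Before unblinding, name one deciding test for VAS pain. One workable statement: the primary analysis is the active-minus-sham difference in VAS at T1, estimated from the planned mixed model, at two-sided alpha 0.05; T2, T3 and T4 are secondary and tested in that order, each only if the preceding test is significant; all other outcomes are reported with 95% confidence intervals as supportive.

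T1 should be defined in words (the assessment on the first day of menstruation after the 20 sessions), because the EEG paragraph uses the same label for a recording after the first session. The fifth-session entry in Statistical analysis should be reconciled with the visit schedule at the same time.

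T1 is not the only sound choice. A single pre-named group-by-time test, used as a gate before any visit is tested, also controls the error when tDCS has no effect at any visit. If that test is itself the deciding one, it should not rely on sphericity. What matters is that one rule is fixed in advance.

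The cost is one paragraph and a registry update. The article describes recruitment as running to April 2026 with assessors blinded, so the change is credible if made before unblinding. The downside of the T1 rule is that an effect seen only at T2 to T4 could not be called the primary result, which the investigators should weigh given their interest in long-term outcomes.

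### The primary VAS model is left open between GEE and a mixed model with its distribution chosen after data collection, the abstract names a third label, and at 17 to 20 women per arm the choice can matter

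*Protocol article*

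**What the plan says.** All of this is in the protocol article.

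- **Statistical analysis, distribution and link:** "After data collection, we will identify the best distribution to represent the data according to the residuals Q–Q plot and histogram". The link function then follows from the distribution of the dependent variable.
- **Statistical analysis, model family:** "The generalised estimated equations or mixed model will analyse the data". This covers primary and secondary outcomes together. No rule says which family applies to which outcome.
- **Statistical analysis, model terms:** time, group and their interaction are the stated factors. Beyond these, "We will also evaluate if it is necessary to insert fixed or random factors into the constant based on" a set of fit indices (printed A/C, B/C and Q/C, evidently AIC, BIC and QIC), a chi-square/df ratio and the intraclass correlation.
- **Statistical analysis, level:** "We will define the significance level in all statistical testing as a p value less than 0.05".
- **Abstract, Methods and analysis:** "A mixed analysis of variance will calculate the effect of stimulation".
- **Sample size:** the trial was sized "through the use of the F-test from a repeated measures analysis of variance".

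The article does not say which covariance estimator or reference distribution a GEE would use.

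**The concern.** A confirmatory trial should have one primary model, fixed before anyone sees the outcomes. Here the model family is an open alternative, the distribution and link depend on the collected data, extra terms depend on fit, and the abstract describes something else. This is not detail left to an analysis plan that is not shown. The article itself states a data-driven procedure, and a plan that fixed one model would contradict it.

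With 34 to 40 women the permitted routes need not agree. The usual GEE robust variance relies on a large number of clusters. With few clusters it is too small, and a chi-square reference ignores its sampling error. A mixed model with finite-sample degrees of freedom does not share that weakness to the same degree. The headline p value could therefore depend on which permitted route is reported.

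**Working it through.** **Inputs from the article.** Alpha is 0.05. There are 20 women per arm randomised and 17 per arm required. Five assessments are scheduled, T0 to T4. The factors are group, time and group-by-time. The interaction therefore has (2 − 1)(5 − 1) = 4 df.

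**The plan's own figure.** The sample size uses "sphericity of 1 and effect size of 0.25". Number of measurements m and correlation ρ are not given. Taking the within-between interaction with λ = f²Nm/(1 − ρ) and df (m − 1) and (N − 2)(m − 1), and assuming m = 2 and ρ = 0.5, λ = 0.0625 × 34 × 2/0.5 = 8.5 and power is 0.807. N = 34 is reproduced. At ρ = 0.5, m = 3, 4 and 5 would give 28, 24 and 22. Adding 6 gives 40. This confirms the arm sizes used below; the sizing is not the point here.

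**GEE with an uncorrected sandwich.** Assume complete normal data, equal covariance in the arms and a saturated group-by-time mean. The sandwich is then each arm's empirical covariance with divisor n, over n, whatever the working correlation. The Wald statistic is W = T² × n/(n − 1), where T² is Hotelling's statistic with ν = 2n − 2. For q df:

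size = P{ F(q, ν − q + 1) > χ²(0.95; q) × [(n − 1)/n] × (ν − q + 1)/(νq) }

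Joint interaction test, q = 4, χ² cut-off 9.488:
- n = 17: 9.488 × 16/17 = 8.930; × 29/128 = 2.023; upper tail of F(4, 29) = **11.7%**
- n = 20: 9.488 × 19/20 = 9.013; × 35/152 = 2.075; upper tail of F(4, 35) = **10.5%**

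Single contrast (one visit against baseline), q = 1, cut-off 3.841:
- n = 17: 3.841 × 16/17 = 3.616; upper tail of F(1, 32) = **6.6%**
- n = 20: 3.841 × 19/20 = 3.649; upper tail of F(1, 38) = **6.4%**

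**Simulation check.** Fitted GEE models (exchangeable, ρ = 0.5, 2,500 null trials per setting) rejected the joint null in 11.2% (n = 17), 10.5% (n = 20) and 11.6% (n = 20 with 15% random dropout). The same fits with the model-based covariance, which was correctly specified, rejected in 5.0% to 5.2%.

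**Sensitivity to the number of visits.** The Statistical analysis section also lists a measurement after the fifth session, which is not among the five scheduled assessments. If it made a sixth time point, q = 5 gives 14.1% (n = 17) and 12.3% (n = 20).

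**Do the candidate remedies work?** Joint tests, complete data:

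| Method | n = 17 | n = 20 |
|---|---|---|
| GEE, Kauermann-Carroll-type variance, chi-square, 4 df | 10.0% | 9.1% |
| GEE, Mancl-DeRouen-type variance, chi-square, 4 df | 8.4% | 7.8% |
| Mixed model, unstructured, Satterthwaite, 3 df (group-by-visit, T1–T4) | 6.2% | 6.0% |
| Mixed model, unstructured, Satterthwaite, 4 df (any group difference, T1–T4) | 7.1% | 6.8% |
| Hotelling-type F reference | 5% | 5% |

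The Satterthwaite rows ignore the baseline covariate and refer T²/q to F(q, ν) instead of the exact F. For example, at n = 17 and q = 3 the critical value is 2.901, × 30/32 = 2.720, and the upper tail of F(3, 30) is 6.2%. Bias correction of the GEE variance alone is therefore not enough, and Satterthwaite is slightly liberal for joint tests.

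**The case against.** The strongest reply is that the 11% belongs to one unstated implementation of one of two permitted models. The article never mentions robust errors or a Wald chi-square, and an article may leave the estimator to the full plan. That stands. A reader might infer that this trial will run at 11% type I error, but the documents do not support it.

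It is also fair that the joint 4-df test is the least favourable case. The article says it will report mean differences with confidence intervals and p values by time point. Those are single-df quantities, for which the excess is about 1.5 percentage points.

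Three further readings go too far:
- **The indices are meant to choose between GEE and the mixed model.** The text cites them for inserting fixed or random factors, and each can be used within its own family.
- **There are three incompatible analyses.** A mixed ANOVA is a mixed model with a compound-symmetric covariance, and the repeated-measures F-test is a planning calculation. What remains is GEE against mixed model, plus an abstract that does not match.
- **Every choice is expressly deferred until the data are in.** The timing phrase governs the distribution, and the link follows from it. That the family is also left until then is inferred from the unresolved alternative.

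Finally, statistical analysis and randomisation are assigned to different researchers, and allocation is known to only one. This reduces the scope for steering the choice. It does not remove it, and it does nothing for a test that is anti-conservative in itself.

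**Conclusion.** The concern holds in a limited form and should be fixed. The article leaves the primary model family open with no rule, makes the distribution, link and extra factors depend on the data, and disagrees with its own abstract.

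The consequence is conditional. Under GEE with uncorrected sandwich errors and a chi-square reference, the nominal 5% becomes about 10.5% to 11.7% for the joint five-visit interaction and 6.4% to 6.6% for one visit against baseline. Under GEE with a correct model-based covariance it stays near 5%. The exact figures assume complete normal data with equal covariance in both arms, and for such data they do not depend on the correlation.

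A reader might add a further inflation from picking the model after seeing results. That is plausible, but nothing in the documents allows a figure for it.

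**What to change.** Before unblinding, name one primary model for VAS in mm: a linear mixed model fitted by REML with group, visit (T1–T4), group-by-visit and baseline VAS, an unstructured covariance and Kenward-Roger degrees of freedom. Satterthwaite is adequate if the primary test is a single prespecified contrast, but is liberal (about 6% to 7%) for joint tests.

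For the primary outcome, delete the GEE alternative, the index-driven search for factors and the distribution choice after data collection. Prespecify one permutation test as the sensitivity analysis for non-normality.

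Where GEE is kept for a non-normal secondary score, pair a bias-corrected variance with a small-sample t or F reference, since the correction alone leaves 7.8% to 10.0% on the joint test.

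Align the abstract with the Statistical analysis section. The cost is a few sentences and negligible analysis work. No design change or extra participants are needed.
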